### Screening for eligibility and enrolment

In Ontario, trained DEC staff will identify potential clients based on the inclusion criteria and then contact them by phone to obtain verbal consent to be contacted by a research assistant (RA). A RA will then conduct an in-home interview to obtain written informed consent and complete the baseline questionnaires. Differing legislation required that study personnel use a different approach in Alberta. First, the recruiter identifies potential clients and then establishes their eligibility and interest. If written consent-to-be-contacted was obtained during recruitment, the client would be contacted by a RA. If there was no written consent-to-be-contacted, then it would be left to the potential client to contact the research team. At the time of recruitment, all eligible clients will be asked to invite their family caregivers (family or friend of at least 18 years of age who provides physical, emotional, or financial care to the client) to participate in the study, and provide their contact information. Participation of a family caregiver is encouraged but not required.

At the initial home visit the RA will first administer the Short Portable Mental Status Questionnaire [48] to assess the client’s mental status. A score of 5 or higher is required for the client to provide consent, and if the client scores below 5, their family caregiver will be invited to consent on behalf of the client. Once the appropriate informed consent has been received, study clients and/or their family caregivers will complete the baseline interview and questionnaires. Interviews and completion of the questionnaires is expected to take about 2 h.

### Program

The RCT is pragmatic, which means that the program will be implemented under real-world conditions, including reliance on existing staff at participating sites. A detailed description of the program is available elsewhere [43]. The program will be delivered by an interprofessional team consisting of RDs and RNs from the participating DECs/PCNs and a program coordinator (PC) from the community partner agencies. As the program is designed to work with the existing personnel within these organizations, there may be additional professionals, such as kinesiologists or pharmacists, who are part of the interprofessional teams. The providers involved in delivering the program in each study site will not provide care to participants randomized to the usual care group. Clients randomly assigned to the control group will continue to be offered usual care services through their local DEC/PCN. The specific services that comprise usual diabetes care vary across both provinces in terms of the length and focus of educational sessions, whether classes are strongly recommended versus optional (e.g., foot care, cardiac health, eating and exercise interventions), access to on-site professionals (e.g., endocrinologist, dietician, physiotherapist, exercise specialist, pharmacist), connections with support services and community resources, and type of follow-up services available.

Clients randomly assigned to the intervention group will be offered the program in addition to the usual care services that they currently receive. The program is a 6-month, multicomponent, client-driven strategy that was designed to support self-management of diabetes and other MCC. It was tested in a pilot study, and was modified based on the feedback received from clients and interventionists [43]. The program consists of the following components: (1) up to three in-home visits by an RN and RD, (2) a monthly group wellness program, hosted by the community partner agency and supported by peer volunteers, (3) monthly case conferences involving the RN, RD, PC, and (3) care coordination and navigation to link clients to other health care professionals and community support services as needed. Because the program is client-driven, there is flexibility in the components in terms of the mode of delivery, specific activities emphasized, and dosage. For example, the client may decline one or more home visits or group sessions, or they may choose the DEC/PCN or alternate setting instead of their home for the visits. A graphical display outlining the intervention versus usual care services is available in Additional file 2 [49].

The fundamental principles underlying the components of the client-driven program are self-efficacy, collaboration, holistic care, and caregiver engagement and support (Table 1). The client is a key member of the care team and is fully engaged in the development of a care plan that is tailored to their individual needs and preferences. The central role of the client is consistent with the current policy priorities of the Ontario [50] and Alberta [51] health ministries. Client self-efficacy, a major determinant of a person’s behavior and motivation to take action, has been found to be a predictor of diabetes self-management [52]. Bandura, the psychologist credited with first recognizing the central role of self-efficacy in behaviour, defined self-efficacy as “the belief in one’s capabilities to organize and execute the courses of action required to manage prospective situations” ([53], p. 2). Key sources of self-efficacy are mastery, social modelling, social persuasion and psychological state such as mood and stress [54]. Various aspects of the program target these sources, including: home visits and group sessions which include education and reinforcement of appropriate self-management principles and activities; group sessions which provide opportunities for social modelling and persuasion; home visits which include motivational interviewing to encourage positive psychological states and celebrate successes by modifying goals and care plans as participants master self-management tasks; and meaningful and inclusive collaboration involving all members of the care team, including clients and their caregivers, to foster their commitment and deeper interest in diabetes self-management.

**Table 1 Tab1:** Principles underpinning the Aging, Community and Health-Community Partnership Program (ACHRU-CPP)

Component	Feature(s)
Self-efficacy	• strengthening confidence of clients and their family caregivers in their abilities to monitor their health, make decisions, and adopt healthy self-care behaviors
Collaborative practice	• involving all members of the care team (interventionists, clients and family caregivers) in all decisions relating to the program • emphasizing flexibility in responses so that individual client preferences can be effectively met • integrating and sharing knowledge from all members of the care team into decisions • optimizing the scopes of practice of the interventionists (e.g., professionals trained in health promotion and prevention can fully utilize these skills, all team members can participate in care planning)
Holistic care	• working with clients to apply self-management principles to the unique set of chronic conditions and risk factors they face (e.g., income, social supports) • developing a care plan that is realistic in view of the client’s strengths, challenges and preferences • integrating evidence-based practices for diabetes with those relating to the other chronic conditions
Caregiver engagement and support	• inviting caregivers to actively participate in home visits, group sessions, and case conferences • incorporating caregiver insights/feedback into the development of a care plan that best meets the client’s needs • ensuring that support services are provided to caregivers to promote their health and wellbeing and assist them in the caregiving role

### Program implementation strategy

A four-pronged approach will be used by the researchers to implement and monitor the delivery of the program at each site to ensure trial adherence:
*Educational workshops*: the investigators will hold training sessions for the interventionists and peer support volunteers before implementation of the program. Each session will be supported with role-appropriate training manuals
*Outreach visits*: the investigators and research coordinators will conduct monthly meetings either in person or by teleconference with the interventionists and peer support volunteers with each of the seven sites to discuss the progress of the study, provide feedback and education, and discuss barriers encountered and possible solutions for identified barriers
*Reminders*: the investigators and research coordinators will provide updates on the study to the interventionists and managers of the participating DECs/PCNs and community partner agencies, including successes and areas for improvement related to the program
*Audit and feedback*: the interventionists will be asked to complete forms (i.e., visit reports and team meeting records) related to program-specific activities that were carried out. At 1-month intervals, the investigators and research coordinators will conduct audits of the study-related documentation to assess fidelity to the program (refer to Additional file 3)

### Participant flow, assessments and timeline

The study involves two assessments: one at baseline (*T*
_1_) and the other 6 months after baseline (*T*
_2_). At baseline, data will be collected on demographic, clinical, and socioeconomic variables in addition to assessment of the primary and secondary outcome variables. The flow of participants through the study phases will be presented using a flow diagram which conforms to the Consolidated Standards of Reporting Trials (CONSORT) guidelines [55] for pragmatic trial reporting (Fig. 3).

**Fig. 3 Fig3:**
[figure not shown]
Flow diagram of progress through study phases

### Sample size

The sample size for the RCT was calculated to detect a minimally important difference (MID) in the primary outcome measure (PCS-12). The developers suggest that the MID for interpretation of group mean PCS-12 score differences is approximately 3.0, which corresponds to an effect size of 0.30 [56]. However, the developers also acknowledge that this MID estimate is a matter of ongoing debate. Robust research on effect sizes seen across a range of studies using a variety of quality-of-life measures has shown that the mean effect size is remarkably consistent at 0.50, or half the standard deviation [57]. This effect size is close to the one observed in our pilot study, which was 0.40 [43].

We based our estimate of the sample size on an effect size of 0.50, 5% alpha, 80% power and 20% attrition (18% was observed in our pilot study). Using these assumptions, the sample size was 80 (each) for the intervention and control groups.

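### The trial is described as sized for the PCS-12 minimally important difference, but the calculation uses 0.50 SD, 1.67 times the only PCS-12 MID it cites (0.30)

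*Protocol article*

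**What the plan says.** All the relevant statements stand in the Sample size section of the protocol article, in this order:

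- The aim: "The sample size for the RCT was calculated to detect a minimally important difference (MID) in the primary outcome measure (PCS-12").
- The benchmark for that outcome: "the MID for interpretation of group mean PCS-12 score differences is approximately 3.0, which corresponds to an effect size of 0.30".
- A caveat: "However, the developers also acknowledge that this MID estimate is a matter of ongoing debate".
- An alternative figure, drawn from studies using various quality-of-life measures, which "has shown that the mean effect size is remarkably consistent at 0.50, or half the standard deviation".
- A link to the pilot: "This effect size is close to the one observed in our pilot study, which was 0.40".
- The calculation: "We based our estimate of the sample size on an effect size of 0.50, 5% alpha, 80% power and 20% attrition", from which "the sample size was 80 (each) for the intervention and control groups".

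Elsewhere, Analysis of participants specifies two-sided tests at 0.05 and a t test on change from baseline to 6 months. Randomization design gives 1:1 allocation. The Abstract puts enrolment at 160 across two provinces, while Participants and setting puts it at 160 in each province.

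**The concern.** A reader who takes the opening sentence at its word will believe that the trial has 80% power for the smallest difference in PCS-12 that matters. The only such difference named for PCS-12 is 3.0 points, and the calculation is not done for it. It is done for 0.50, which the text describes as a mean effect size across measures and does not present as an MID for PCS-12. The pilot is offered as support, but at 0.40 it also lies below the design value. Both figures specific to this outcome or this programme are therefore smaller than the one used.

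This matters for interpretation. PCS-12 change is the primary outcome and is judged by a two-sided 5% test. If the trial is believed to have been sized for the MID, a non-significant result could be taken as evidence that no important benefit exists, when the design may have had a modest chance of detecting one.

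**Working it through.** **Inputs.** Effect sizes 0.50 (design), 0.40 (pilot) and 0.30 (cited MID), 80% power, 20% attrition and 80 per arm, all from Sample size. Two-sided alpha 0.05 and a two-sample t test on change, from Analysis of participants. 1:1 allocation, from Randomization design.

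**1. Reproduce the plan's figure.** The normal approximation is n per arm = 2(1.96 + 0.8416)² / d². With d = 0.50 this gives 62.8, so 63. The t test gives 63.77, so 64. Allowing for attrition, 64 / (1 − 0.20) = 80 per arm. The stated figure is reproduced.

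**2. Compare the design effect with the cited figures.** 0.50 / 0.30 = 1.67. If 3.0 points equals 0.30 SD, the implied SD is 3.0 / 0.30 = 10 points, so 0.50 SD is about 5 points. Required sample size scales with 1/d². Moving from 0.50 to 0.40 multiplies it by (0.50 / 0.40)² = 1.56, which is a large change for two values described as close.

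**3. Power at each effect size.** Approximately, power = Φ(d·√(n/2) − 1.96). With n = 64 and d = 0.30, this is Φ(0.30 × 5.657 − 1.96) = Φ(−0.263) = 39.6%. The t test gives 39.2%. The t-test results are:

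| Evaluable per arm | d = 0.50 | d = 0.40 | d = 0.30 |
|---|---|---|---|
| 64 (160 randomised, 20% attrition) | 80% | 61% | 39% |
| 80 (160 randomised, no attrition) | 88% | 71% | 47% |
| 128 (320 randomised, 20% attrition) | 98% | 89% | 67% |

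**4. Size of the gap.** For 80% power by t test with 20% attrition, d = 0.40 needs 100 evaluable, and 100 / 0.8 = 125 per arm (250 in total). d = 0.30 needs 176 evaluable, and 176 / 0.8 = 220 per arm (440 in total). These totals show the distance from 160. They are not a proposal to enlarge the trial.

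**5. Sensitivity to the unit of the effect size.** Steps 3 and 4 treat each effect size as standardised on the SD of the variable tested, as the section's own calculation does. If 0.30 is instead in units of the raw-score SD, the effect on the change score is d / √(2(1 − ρ)), where ρ is the baseline-to-6-month correlation. The document gives no ρ, so the range below is an assumption. The 95% CI half-width is 1.96 × 10 × √(2(1 − ρ)) × √(2/64).

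| Assumed ρ (64 per arm) | Power at 0.30 | Power at 0.40 | Half-width, points |
|---|---|---|---|
| 0.5 | 39% | 61% | 3.5 |
| 0.6 | 47% | 71% | 3.1 |
| 0.7 | 59% | 83% | 2.7 |
| 0.8 | 76% | 94% | 2.2 |

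At ρ = 0.5 the change-score SD equals the raw SD, so the first row matches step 3. The smallest effect with 80% power at 64 per arm is 0.499. On this reading, the cited MID reaches 80% power only when 0.30 / √(2(1 − ρ)) = 0.499, that is ρ = 1 − (0.30 / 0.499)² / 2 = 0.82. The pilot effect reaches it at ρ = 1 − (0.40 / 0.499)² / 2 = 0.68.

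**The case against.** The strongest defence is that nothing is hidden and nothing is miscalculated. The section reports the developers' 3.0 points, says the value is debated, gives a reason for preferring half a standard deviation, and states plainly that 0.50 was used. It can be read as a choice between two benchmarks. This stands as far as it goes: the choice is disclosed and the arithmetic is right. It does not rescue the opening sentence, because the text names no other MID for PCS-12 and describes 0.50 only as an average effect size.

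A second objection also stands. The 39% and 61% rest on two conditions that the document does not settle: a total of 160, and effect sizes standardised on the analysed change score. With 320 pooled, power at the pilot effect is 89% and that part of the concern falls away; power at 0.30 is 67%, still short of 80%. With raw-score units and a high correlation, power is considerably better.

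A reader might infer that the interval will always be too wide to exclude 3.0 points, even around an estimate of zero. The document does not support that. The half-width of 3.5 points needs a change-score SD of 10, and at an assumed correlation of 0.7 it is 2.7 points.

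Finally, Analysis of participants already promises effects with 95% confidence intervals, and nothing in the article says that a null test will be reported as no effect. The risk is one of interpretation, not a planned misuse.

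**Conclusion.** The concern holds as a misstated design property. The section claims sizing for an MID in PCS-12, but the calculation targets an effect 1.67 times the only PCS-12 MID it cites, and describing 0.50 as close to 0.40 understates a 56% difference in required sample size.

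On the section's own standardised basis with 160 in total, power is 80% at 0.50, 61% at 0.40 and 39% at 0.30. With 320 pooled it is 98%, 89% and 67%. With raw-score units, 64 evaluable per arm and an assumed correlation of 0.5 to 0.8, it is 39% to 76% at 0.30 and 61% to 94% at 0.40. In each of these cases power at the cited MID stays below 80%. That would change only with a correlation above about 0.82 on the raw-score reading with 160 patients, or a lower one with 320.

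Two stronger readings are tempting and should be resisted. One is that the sample size is wrongly calculated; it reproduces exactly. The other is that 39% is the trial's established power for an important effect. That figure is conditional, and the text itself treats the 3.0-point threshold as debated. The number of patients, the test and the outcome need not change, so this is a point that should be fixed, not one that must be fixed before the trial can be relied on.

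**What to change.** Leave the number of patients to be recruited as it is and revise the text:

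- Replace the claim of sizing for the MID with a statement that 80 per arm (64 evaluable) gives 80% power for an effect of 0.50 SD.
- State the lower power at the pilot effect of 0.40 and at the cited MID of 0.30. Name the SD to which the effect sizes refer and, if it is the raw-score SD, the correlation assumed, with a range.
- Delete the description of 0.50 as close to the pilot value.
- Reconcile the total enrolment in the Abstract with that in Participants and setting, and tie the power statement to the reconciled figure.
- Commit to reading the primary 95% confidence interval against 3.0 points, so that a non-significant test is not reported as absence of an important effect.

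The cost is rewording one section, correcting one enrolment figure and adding a sentence on interpretation. The drawback is a less favourable power statement.

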### Randomization design

After providing written, informed consent and completing the baseline questionnaires, participants will be randomly assigned to either the intervention or the control arm of the study using a 1:1 allocation ratio. Stratified permuted block randomization will be used to assign participants to the control and intervention groups. Study sites are expected to be relatively homogeneous regarding client sociodemographic and clinical characteristics and the delivery of intervention and usual care services. However, to minimize the confounding effects of possible differences among the study sites, the sites will be used as a stratum. The randomized sequence at each site will be based on assignments of blocks randomly selected from sizes of 2, 4, or 6. A biostatistician not involved in the recruitment process will generate the random number assignments for each site using SAS Version 9.3. Random number sequences will be input into a centralized web-based randomization service (REDCap) that will allocate clients to the control or intervention group at each site in accordance with the sequence.

### Blinding

After randomization, the interventionists and clients will know the group assignments. This lack of blinding is unavoidable; however, efforts will be made to blind the assessors who conduct the 6-month assessment. Some unblinding may occur, for example, if a client describes a home visit or group session in their interview with the assessor, even if such information is not requested. The statistician/data analyst will be blinded to the group assignments.

#### Analysis of clinical effectiveness

##### Outcome measures

Table 2 describes the primary and secondary outcome measures used to evaluate clinical effectiveness. The primary outcome is the change in Physical Component Summary (PCS-12) score from the short form-12v2 health survey (SF-12) [58]. The SF-12 is a generic quality-of-life instrument that is well-validated and able to distinguish between groups of clients with known clinical differences in a variety of populations [58]. The pilot study supported the selection of the PCS-12 score as the primary outcome by demonstrating that the PCS-12 was responsive over the 6-month intervention period and grounded in questions that were easily interpreted by the older adult clients [43]. The PCS-12 is also a common primary outcome in studies evaluating programs similar to ours [59] and focuses on an outcome (physical functional ability) that is important to clients [60]. Secondary outcomes include the change in the following variables from baseline (*T*
_1_) to 6 months (*T*
_2_): Mental Component Summary (MCS) score from SF-12 [61]; Center for Epidemiological Studies Depression Scale (CES-D-10) [62–65]; Generalized Anxiety Disorder 7-item scale (GAD-7) [66–70]; Summary of Diabetes Self Care Activities (SDSCA) [71, 72]; and the Modified Caregiver Strain Index (CSI) [73].

**Table 2 Tab2:** Effectiveness outcomes, target population, and analysis

Effectiveness outcomes				
Variable/outcome	Hypothesis	Measure	Group(s)^a^	Method of analysis
Physical functioning	Improve more in the intervention group	Physical Component Summary (PCS-12) [58]	CT, CG	Means and standard deviations, *t* tests for comparing change from baseline (*T* _1_) to 6 months (*T* _2_) in the intervention and control groups ANCOVA analysis to explore predictors of primary outcome multiple regression with backward selection to explore impact of dose on primary outcome
Mental functioning	Improve more in the intervention group	Mental Component Summary (MCS) from SF-12 [61]	CT, CG	
Depressive symptoms	Larger reduction in the intervention group	Center for Epidemiological Studies Depression Scale (CES-D-10) [62–65]	CT, CG	
Anxiety	Larger reduction in the intervention group	Generalized Anxiety Disorder 7-item Scale (GAD-7) [66–70]	CT	
Self-management	More improvement in the intervention group	Summary of Diabetes Self Care Activities (SDSCA) [71, 72]	CT	
Self-efficacy	More improvement in the intervention group	Self-Efficacy for Managing Chronic Disease 6-item scale [52, 74–81]	CT	
Caregiver strain	Larger reduction in the intervention group	Modified Caregiver Strain Index (CSI) – 13 items [73]	CG	
Interprofessional team collaboration	Improvement in collaboration over 6 months in the intervention group	Team Climate Inventory (TCI) [82–84]	INT	

Demographic data will be collected from all participant groups. All clients will be asked to provide their age, gender, education, and diabetes history (duration, family history). Clients and family caregivers will also be asked to provide household income, marital status, and comorbid health conditions. Caregivers will be asked to provide their employment status and ethnic back ground. Interventionists will be asked about the number of years working in their field and the number of years in their current role

^a^Three groups: *CT* client, *CG* caregiver, *INT* interventionists (e.g., RN, RD, PC)

To better understand the mechanisms underlying the changes in primary and secondary outcomes, changes from baseline (*T*
_1_) to 6 months (*T*
_2_) in the following measures will be assessed: (1) Self-Efficacy for Managing Chronic Disease 6-item scale [52, 74–81]; items in the scale are common across many chronic diseases, including symptom control, role function, emotional functioning and communicating with physicians, and (2) Team Climate Inventory (TCI) [82–84] (19-item); that includes participative safety (trust in group members), support for innovation (openness to new ideas), vision (shared goals and valued outcomes), and task orientation (shared concern for excellence) is evaluated.

